### Treatment as usual

Participants in both conditions will receive treatment as usual from hospital clinicians. At a minimum, this will consist of antipsychotic pharmacotherapy and a therapeutically safe and secure environment appropriate to the individual patient’s needs [76–78] however most patients are expected to be involved in a range of therapies provided by multidisciplinary team members, including psychiatrists, clinical psychologists, psychiatric nurses, occupational therapists and social workers [78].

Medication will be managed separately by the consultant psychiatrists responsible for the patients’ care and may change over the duration of the study as required. Both antipsychotic dose and anticholinergic burden will be measured at each assessment point as these may be important treatment moderators [79].

The number of routine therapeutic hours each patient receives in the treatment as usual (control) and the cognitive remediation group will be recorded from patient’s progress notes/ medical charts each week. A narrow definition of therapeutic activity will be applied to prevent over inclusion: a therapy will be defined as any activity that is occurring on a consistent or regular basis targeting specific goals and designed to address patients’ forensic mental health needs. From this perspective regular occupational therapy, cognitive behavioural work, psycho-education, harmful behaviour programmes, substance misuse interventions, group programmes etc. would be defined as therapeutic activities, in contrast multidisciplinary team meetings, general interviews or assessments, physical exercise and general vocational or educational work will not be seen as therapies.

### Assessment battery

All assessors will complete a training programme prior to administering study related assessments. For assessments that require clinical judgment (e.g. symptom severity measures), assessors will observe a number of interviews carried out by an experienced consultant psychiatrist whilst simultaneously rating patients' performance. The inter-rater reliability of assessors will also be measured as part of the training programme for assessors. Primary and secondary outcome measures are presented in Table 2.

**Table 2 Tab2:** Outcome Measures

Primary Outcome Measure	MATRICS Consensus Cognitive Battery Composite Score (MCCB)
Secondary Outcome Measure	MCCB Domain Scores
	Social cognitive assessments
	• The Reading the Mind in the Eyes Test
	• The Faux Pas Recognition Test
	• The MSCEIT
	Social and Occupational Functioning Assessment Scale (SOFAS)
	Positive and Negative Syndrome Scale (PANSS) – negative and disorganised scales
	Clinical assessment interview for negative symptoms (CAINS)
	Historical Clinical Risk -20 (HCR-20)
	DUNDRUM-3 Programme Completion Scale
	DUNDRUM-4 Recovery Scale
Validity Checks	Rate of enrolment, rate of retention, rate of completion of primary outcome measures, success of blinding.
Patient satisfaction survey	Service user developed interview.

### Primary outcome measure: change in global cognitive functioning

Cognitive functioning among study participants will be assessed at baseline, end of treatment (approximately 6 months) and 8 month follow up using the MATRICS Consensus Cognitive Battery (MCCB) global composite score [61]. The MATRICS battery covers seven cognitive domains: processing speed; attention/ vigilance; working memory; verbal learning; visual learning; reasoning and problem solving; social cognition assessed using social reasoning tasks for understanding and managing emotions taken from the Managing emotions subtest of the Mayer-Salovey-Caruso Emotional Intelligence Test (MSCEIT) which is a social reasoning test. The test comprises of vignettes of various situations, and options for coping with the emotions depicted in these vignettes [80, 81]. Participants are required to indicate the effectiveness of each solution ranging from one (very ineffective) to five (very effective). In validation studies, and in antipsychotic trials of stable patients, the MATRICS demonstrated excellent reliability, minimal practice effects and significant correlations with measures of functional capacity. It is hypothesised that there will be a group by time interaction (CRT vs TAU) on the total score of the MATRICS battery at the end of treatment approximately 6 months and at 8 months follow up.

### Secondary outcome measures

#### Change in specific cognitive domains

The MATRICS battery will also be used to assess change in specific cognitive domains for study participants. The processing speed, attention/ vigilance, working memory, visual learning, verbal learning, reasoning/ problem solving and social cognitive domains of the MATRICS battery will all be used as secondary outcome measures. It is hypothesised that there will be a group (CRT vs TAU) by time interaction on the MATRICS domain scores at the end of treatment and eight month follow up [61]

### Social cognitive measures

Changes in social cognition will be assed using The Reading the Mind in the Eyes Test [62], the Faux Pas Recognition Test [63] and the Managing Emotions subtest of the Mayer-Salovey-Caruso Emotional Intelligence Test (MSCEIT). It is hoped that each of these tests will tap into different components of the emotional processing stream [40]. The Reading the Eyes of the Mind Test will measure emotional perception as well as theory of mind, the Faux Pas Recognition Test will measure the participants awareness of emotional context or social sensitivity, and finally the MSCEIT is a measure of social as well as emotional reasoning.

### Real world functioning

Secondary outcome measures will include the Social and Occupational Functioning Assessment Scale (SOFAS) [64]. The SOFAS is a continuous scale (0–100) with verbal tethers so that higher scores represent superior functioning. It is similar to the Global Assessment of Functioning Scale however it does not include the severity of psychiatric symptoms. Again it is hypothesised that there will be a group (CRT vs TAU) by time interaction at the end of treatment and eight month follow up.

### Psychiatric symptoms

Secondary outcome measures will also include the scores on the disorganised and negative symptoms scales from the five factor Positive and Negative Syndrome Scale (PANSS) and the total score from the Clinical Assessment Interview for Negative Symptoms (CAINS) [67, 68]. The PANSS contains 30 items measuring psychopathology associated with schizophrenia, 7 items assess positive symptoms, seven items assessing negative symptoms and 16 items assess general psychopathology. A five factor model of the PANSS will be used to evaluate outcomes because CRT is thought to have a specific impact on negative and disorganised symptoms [82]. The CAINS is a 13 item interview for measuring negative symptoms associated with schizophrenia. It contains 9 items for assessing problems with motivation and pleasure and 4 items for assessing problems with emotional expression. Again it is hypothesised that there will be a group (CRT vs TAU) by time interaction at the end of treatment and eight month follow up.

### Violence risk

Violence risk will be assessed with the Historical and Clinical Risk Management Scale 20 (HCR-20) a measure of violence risk, sometimes referred to as violence proneness [51]. The HCR-20 is among the most widely used violence risk assessment schemes. The HCR-20 contains ten historical or static items, five current or clinical items and five future risk items. Both the clinical and risk items are thought to be dynamic in nature in that they can change over time and are amenable to therapeutic intervention. Because the historical items are static in nature only the dynamic items will be used as a secondary outcome measurement. Violence risk will only be measured at baseline and eight month follow up. Again it is hypothesised that there will be a group (CRT vs TAU) by time interaction. The HCR-20 will be rated approximately every six months by the treating multi-disciplinary team and researchers.

### Programme completion and recovery

It is hoped that there will be differences between participants receiving CRT compared to TAU on their ability to benefit from additional psychosocial treatment programmes offered. Participant ability to benefit from additional psychosocial treatment will be assessed with the Dundrum-3 Programme Completion scale rated by psychiatric registrars and by patients’ multidisciplinary teams blind to the intervention [78]. The Dundrum-3 is a structured clinical judgment instrument which assesses whether patients have participated in, engaged and benefited from psychosocial programmes and consists of seven items: physical health, mental health, drugs and alcohol, problem behaviours, self-care and activities of daily living, education occupation and creativity and family and social networks. Each item is rated on a five point scale with lower scores representing a higher level of participation and engagement. Patient ability to recover within a forensic setting will be assessed with the Dundrum-4 Recovery Scales [78]. The Dundrum 4 contains six items: stability, insight, therapeutic rapport, leave, dynamic risk and victim sensitivity. Similar to the DUNDRUM-3 Programme Completion Scale, each item of the DUNDRUM-3 is also rated on a five point scale with lower scores representing greater progress towards recovery. The Dundrum-3 Programme Completion Scale has been shown to significantly distinguish between levels of security within a forensic setting and the Dundrum-4 Recovery Scale has been shown to distinguish those given unaccompanied leave outside of a secure forensic setting. Programme completion and recovery will only be measured at baseline and eight month follow up. Again it is hypothesised that there will be a group (CRT vs TAU) by time interaction.

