### Randomisation and treatment allocation

Upon enrolment in the study participants will be randomised to cognitive remediation and a waiting list control group receiving treatment as usual (TAU) by the clinical director of the Central Mental Hospital using ‘select cases’ ‘random samples’ (select cases random number generator) function in SPSS V21 [56]. Fig. 1 is a CONSORT diagram outlining patient allocation. Patients randomised to receiving TAU will be offered the intervention upon completion of the study. The clinicians conducting the therapy sessions will be different from the research team carrying out the assessments. The sequence of randomisation will be concealed from the research team carrying out the baseline and outcome assessments i.e. blinded assessment. All participants will be trained not to reveal their study condition prior to each follow up assessment. Should the blind be broken this will be noted. Furthermore all assessors will be asked to guess whether participants were receiving TAU or CRT for each of the follow up assessments to see if they perform at a chance level of accuracy. Patient participation in CRT will be shared with their treating psychiatrist. The socio-demographic characteristics of the cognitive remediation group and the waiting list control group will then be compared on a range of measures e.g. age, sex, dose of antipsychotic medication (expressed as chlorpromazine equivalents) [57–59], pre-morbid IQ (estimated from TOPF^uk^) [60], MATRICS global composite scores, MATRICS domain scores, Social Cognitive Scores [60–62], real world functioning (SOFAS), psychiatric symptoms (PANSS), negative symptoms (CAINS) and violence proneness (HCR-20) [63–66].

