In practical terms each session will involve practicing discreet cognitive functions identified by the MATRICS consensus cognitive battery [63] e.g. attention, working memory, verbal memory, visual memory, comprehension, problem solving and social cognition. A variety of pen and paper materials will be used to achieve this aim. A free open source version of the Dual N-back computer programme (http://brainworkshop.sourceforge.net) will also be used to help patients develop and modulate their attentional recourses in addition to their working memory (visual and spatial) and processing speed. Over the course of the intervention as patients make progress the cognitive remediation procedures will gradually increase in difficulty.

The cognitive remediation will be delivered by Masters’ level assistant psychologists and the cognitive remediation support group will be delivered by multidisciplinary professionals including psychiatric registrars, occupational therapists and psychiatric nurses. All therapists contributing to the cognitive remediation programme will attend a three day training course prior to delivering the intervention. All therapists will attend weekly supervision sessions where fidelity to the treatment principles will be actively monitored. Fidelity to the treatment will also be assessed by observing adherence to the nine treatment principles during randomly selected individual and group treatment sessions.

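### DUNDRUM-3 is declared blind-rated, but its raters come from clinical teams and staff groups that are told of CRT participation or deliver CRT, and no rule keeps them apart

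*Protocol article*

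**What the plan says.** Five places in the protocol article bear on who rates these outcomes and what they know.

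- **Programme completion and recovery.** DUNDRUM-3 is "rated by psychiatric registrars and by patients’ multidisciplinary teams blind to the intervention". DUNDRUM-4 is described in the same section without a named rater. Both are measured at baseline and eight months only.
- **Randomisation and treatment allocation.** "Patient participation in CRT will be shared with their treating psychiatrist". The safeguards in this section are that "The clinicians conducting the therapy sessions will be different from the research team carrying out the assessments" and that "The sequence of randomisation will be concealed from the research team carrying out the baseline and outcome assessments i.e. blinded assessment".
- **Treatment as usual.** Care comes from "multidisciplinary team members, including psychiatrists, clinical psychologists, psychiatric nurses, occupational therapists and social workers".
- **Cognitive remediation operationalised by nine treatment principles.** The therapists' paragraph says that "the cognitive remediation support group will be delivered by multidisciplinary professionals including psychiatric registrars, occupational therapists and psychiatric nurses".
- **Violence risk.** "The HCR-20 will be rated approximately every six months by the treating multi-disciplinary team and researchers". This section does not mention blinding.

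**The concern.** A blinding claim is a statement about what particular raters know. Here the raters are registrars and the patient's own team. The article tells one member of that team who is receiving CRT, and it draws the support-group leaders from the same professions. The only separation it sets up is around the research team, to which these raters are not said to belong.

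DUNDRUM-3 is a structured judgement of how far a patient has taken part in and gained from programmes, so a rater's expectation can move the score. The Hypotheses section counts programme participation, recovery and dynamic violence risk as part of functioning under the first aim, and the Discussion rests much of its public-protection argument on improved programme benefit and functioning. If a difference appeared on DUNDRUM-3, a report following the article's wording would call it blind-rated. A reader could not then separate a treatment effect from rater expectation, and no later analysis could repair that.

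**Working it through.** The plan gives no figure on this point, so the main check is to set the passages side by side. A short calculation then shows scale.

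**1. Who rates, and what the article says they know**

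| Rater | Outcome | Stated to be blind? | What the article says elsewhere |
|---|---|---|---|
| Treating psychiatrist, as team member | DUNDRUM-3 | Yes | Told of CRT participation: contradicted |
| Rest of the patient's team | DUNDRUM-3 | Yes | Not expressly told; share a team with someone who is; nurses and occupational therapists also staff the support group |
| Psychiatric registrars | DUNDRUM-3 | Yes | Registrars are among those who deliver the support group |
| Treating team and researchers | HCR-20 | Not stated | Team as above; researchers covered by concealment if they are the assessment team; analysed rating not specified |
| Not named | DUNDRUM-4 | Not stated | Affected only if rated like DUNDRUM-3 |
| Research team | MCCB (primary) | Yes | Separate from therapists, sequence concealed: consistent |

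**2. Do the safeguards reach the clinical raters?** Both sentences name the research team. Neither mentions registrars or treating teams, and nothing stops someone who treats a patient, or leads that patient's support group, from rating that patient.

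**3. Illustration of size**

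Inputs:
- About 60 patients (Participants section), taken here as 30 per arm; equal split is an assumption.
- Two-sided alpha 0.05 (Proposed analysis).
- r = correlation between baseline and follow-up scores. The article gives at least .5, but for the MCCB composite; applying .5 to these scales, and trying .7, are both assumptions.
- b = net rater tilt in favour of CRT at follow-up, in SD units of the outcome. The documents give no value; 0.1 to 0.3 is an assumed range.
- No true effect; age and gender covariates ignored.

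With two time points, the group-by-time interaction is the two-sample t-test on change scores.

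- SD of change = √(2(1 − r)): 1.000 at r = .5 and 0.775 at r = .7.
- SE of the difference = SD of change × √(2/30): 0.258 and 0.200.
- Noncentrality = b / SE. For b = 0.2: 0.2/0.258 = 0.775 and 0.2/0.200 = 1.00.
- Rejection rate = probability that a noncentral t on 58 degrees of freedom falls outside ±2.002.

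| Tilt b | r = .5 | r = .7 |
|---|---|---|
| 0 | 5% | 5% |
| 0.1 SD | 6.7% | 7.8% |
| 0.2 SD | 11.9% | 16.6% |
| 0.3 SD | 20.8% | 31.4% |

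**The case against.** The strongest reply is that the documents show much less than full unblinding, and most of it stands.

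- **A reader might infer that the whole team cannot be blind.** Only the treating psychiatrist is expressly told. Knowledge among colleagues is plausible, but it is inferred.
- **A reader might infer that the same people deliver CRT and rate its recipients.** The article names professions, not individuals. It fails to prevent overlap; it does not establish it.
- **A reader might infer that the charts reveal allocation.** The Treatment as usual section has routine therapy hours extracted from notes. It does not say that CRT sessions are entered there.
- **A reader might infer that attending CRT will itself be scored as success on DUNDRUM-3.** The section frames the target as benefit from *additional* programmes, which points away from counting CRT. An explicit scoring rule may sit in the full protocol, so its absence from the article is not an error.
- **A reader might call HCR-20 a second contradiction.** It is never called blind, and researchers take part in rating it. The sentence may mean separate scores or one joint score.
- **Checks on the blind exist.** Participants are trained not to disclose, breaks are noted, and assessors guess the allocation at each follow-up. Whether these checks extend to clinical-team raters is unclear. In any case they measure unblinding, and they do not remove a disclosure that is built into the design.

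None of this reconciles the declared blinding of the team's ratings with the planned disclosure to one of its members.

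**Conclusion.** The point holds for DUNDRUM-3. The article attributes blinding to clinical-team ratings; its own disclosure rule contradicts this for the treating psychiatrist, and its staffing of the support group undercuts it for registrars, nurses and occupational therapists. For HCR-20 the problem is different: blinding is not stated and the rating to be analysed is not identified. DUNDRUM-4 is affected only if it is rated in the same way as DUNDRUM-3.

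The documents cannot give the size of any bias. On the assumptions above, a tilt of 0.2 SD would take the false-positive rate from 5% to about 12% or 17%, which shows only that a modest tilt would matter in a trial of this size.

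Severity is moderate. Only secondary outcomes are involved, and the blinded assessment of the MCCB composite is untouched. What changes is how far the trial can claim a blind-rated effect on programme completion.

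**What to change.** 1. Have DUNDRUM-3 and DUNDRUM-4 outcome ratings made by the blinded research assessors, or by existing registrars who neither treat the patient nor run the support group. Name the rater for DUNDRUM-4.
2. State whose HCR-20 rating is the outcome. Use the blinded researchers' rating if it is scored separately from the team's.
3. State that CRT and its support group do not count when DUNDRUM-3 is scored. This makes the stated focus on *additional* programmes operational.
4. For any rating still made by the treating team, delete the claim of blinding and report the result as unblinded and supportive.

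These changes leave the disclosure to the treating psychiatrist as it is. The cost is some reassigned rating work for about sixty patients at two time points, with raters who know the patients less well than their own teams do. If reassignment is not feasible, the fourth change alone removes the contradiction for DUNDRUM-3, at the price of a weaker claim.

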### Patient satisfaction measure

An interview developed by service users will be used to explore patient satisfaction with cognitive remediation [45]. The interview will inquire about the following areas: 1) task difficulty, 2) experience of sessions, 3) relationship with therapist and 4) impact of CRT on daily life. The interview will be administered by a social worker who will be independent of treatment and assessment teams, to the intervention and to other assessments. Patients will be reassured that their responses will be anonymously recorded i.e. that their names will not be connected with the feedback they provide.

### Proposed analysis

Data analysis will be carried out using an intention to treat methodology [83]. Data from all enrolled participants will therefore be used in the analysis regardless of their level of participation in the study. Missing data will be estimated using multiple imputation [84]

The interaction between time i.e. baseline vs. 6 month and treatment condition (CRT vs TAU) on our primary outcome variable (MCCB composite cognition score) will be examined rather than between group differences, because tests of group difference average Time 1 (baseline) and Time 2 (6 month) assessments across the groups and consequently will be less sensitive to change. The interaction between time and treatment condition will be assessed using a repeated measure ANOVA with age and gender entered as covariates. This analysis will also be repeated at follow up using all three data points.

An a priori estimate of statistical power was completed using G*Power 3.1 [85]. Assuming a correlation greater than or equal to .5 between baseline and 6 month MCCB composite and a medium effect size (i.e. f = .25), the power to detect a statistically significant interaction between time and treatment conditions (i.e. CRT vs TAU) is adequately powered i.e. greater than or equal to .80. Should we find a statistically significant time X treatment condition interaction, post-hoc probing of the interaction will be completed with Bonferroni corrections applied where appropriate to maintain an alpha of 0.05.

SPSS PROCESS Macro Model 4 will be used to explore mechanisms of action should we find a positive impact of CRT. For example, whether change in cognition leads to a change in functioning, or whether a change in negative symptoms leads to a change in functioning etc. Change score will be calculated by subtracting the scores at baseline from the sores following the intervention. Age and gender will be entered as covariates in all mediation analysis. Bootstrapping will be used to estimate indirect effects, and 95 % bias-corrected confidence intervals using 1,000 bootstrap samples will be applied. A confidence interval that does not contain zero indicates statistically significant mediation (*p* < 0.05).

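### The primary test leaves baseline MCCB out as a covariate and so gives up efficiency: one third more patients at r = .5, 5% at r = .9 (free improvement)

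*Protocol article*

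**What the plan says.** All of this is in the protocol article, mostly under Proposed analysis.

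- **Estimand of the primary test:** "The interaction between time i.e. baseline vs. 6 month and treatment condition (CRT vs TAU) on our primary outcome variable (MCCB composite cognition score") is what will be examined, in preference to a difference between groups.
- **Reason given:** group comparisons are set aside "because tests of group difference average Time 1 (baseline) and Time 2 (6 month) assessments across the groups", which in the plan's view makes them worse at detecting change.
- **Model:** the interaction "will be assessed using a repeated measure ANOVA with age and gender entered as covariates". Baseline MCCB is not among the covariates. The same analysis is repeated at follow-up with all three time points.
- **Power statement:** the correlation enters as "Assuming a correlation greater than or equal to .5 between baseline and 6 month MCCB composite"; the effect to be detected is given as "a medium effect size (i.e. f = .25"). With these inputs the interaction test "is adequately powered i.e. greater than or equal to .80".
- **Baseline data:** under Randomisation and treatment allocation, the arms are to be compared at baseline on a list of measures that includes "MATRICS global composite scores, MATRICS domain scores". The baseline composite is therefore available for every assessed patient.

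**The concern.** With two time points, the time-by-treatment interaction is the difference between arms in mean change, and its 1-df F is the square of the t-test on change scores. The plan reaches this test by setting aside one alternative, the between-subjects main effect, which does mix baseline with 6 months. It does not consider the usual alternative for a randomised trial with a baseline measurement: the 6-month score compared between arms, with the baseline score as covariate (ANCOVA).

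Two things are at stake. The first is precision, in a single-centre trial of about sixty patients where further recruitment would be hard. The second is how the estimate behaves if the arms differ at baseline by chance. A change score subtracts the whole baseline difference, although only a fraction r of it is expected to persist to 6 months.

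**Working it through.** **Inputs.** N of about 60 (Participants); r at least .5 and f = .25 (Proposed analysis); d of about 0.5 on cognition, from the meta-analysis cited in the Background section on cognitive remediation therapy. Assumptions: 1:1 allocation (30 per arm; no ratio is stated), two-sided alpha .05 for the primary test (the document states .05 only for post-hoc probing), and equal SDs at both times.

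**Step 1: the plan's own power figure.** The G*Power default for a within-between interaction with m = 2 measurements uses noncentrality λ = N·m·f²/(1 − r) = 60 × 2 × 0.0625 / 0.5 = 15, on 1 and 58 df. Power is .968, and 34 patients would give .80. The claim of at least .80 is reproduced. Taking 2 further df for age and gender leaves it at .968. In this convention f = Δ/(4 SD), so f = .25 corresponds to a between-arm difference in change of Δ = 1.0 SD. The document does not name the effect-size option; under the program's SPSS-type option the same inputs would give about .47 to .48.

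**Step 2: variances.** Per patient, in units of σ²:

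- change score: 2(1 − r)
- ANCOVA: 1 − r²
- difference: 2(1 − r) − (1 − r²) = (1 − r)², which is never negative
- ratio of ANCOVA to change: (1 + r)/2, so the change analysis needs 2/(1 + r) times the patients

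| r | (1 + r)/2 | Extra patients for change analysis |
|---|---|---|
| .5 | .75 | 33% |
| .6 | .80 | 25% |
| .7 | .85 | 18% |
| .8 | .90 | 11% |
| .9 | .95 | 5% |

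At r = .5, ANCOVA on 60 patients is worth 60/.75 = 80 patients analysed by change.

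**Step 3: power at N = 60.** λ = (N/4)·d²/V, with V the variance from Step 2; 58 df for change, 57 for ANCOVA.

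| Effect | r | λ change | λ ANCOVA | Power change | Power ANCOVA | N for .80 (change / ANCOVA) |
|---|---|---|---|---|---|---|
| 1.0 SD (plan's f = .25) | .5 | 15 | 20 | .968 | .993 | 34 / 26 |
| 0.5 SD (cited effect) | .5 | 3.75 | 5.00 | .48 | .59 | 128 / 98 |
| 0.5 SD | .7 | 6.25 | 7.35 | .69 | .76 | 78 / 68 |
| 0.5 SD | .8 | 9.38 | 10.42 | .85 | .89 | 54 / 48 |

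At r = .5 even the unadjusted 6-month comparison has V = 1, the same as change, and hence the same power (.478 at d = 0.5). So group comparisons are not, as a class, less sensitive than the interaction.

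**Step 4: simulation check.** 6,000 trials per setting, N = 60, with age-type and gender-type covariates in both models. The variance ratio, change over ANCOVA, was 1.30 to 1.32 at r = .5 and 1.08 at r = .8. Type I error was .047 (change) and .048 (ANCOVA). With a true effect of 0.5 at r = .5, both mean estimates were 0.50. The simulated covariates were unrelated to the outcome, so this checks the formulas in a small sample. It does not show what a prognostic age effect would do. Strictly, the r that matters is the correlation left after age and gender.

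**Step 5: chance imbalance.** The standard error of the baseline difference is √(2/30) = 0.26 SD. Given a baseline imbalance of that size, the change estimate is shifted by (1 − r) × 0.26: 0.13 SD at r = .5, about a quarter of an effect of 0.5 SD, and 0.05 SD at r = .8. The shift runs against the arm that starts higher. ANCOVA removes it.

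**The case against.** **The stated reason is correct in its own setting.** Within a repeated-measures ANOVA, the group test is the main effect, and that does average the two occasions. This stands. The sentence is incomplete rather than false: it disposes of the main effect and leaves the baseline-adjusted comparison unaddressed.

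**One third is the worst case.** It applies at the floor of the plan's range for r. The Primary outcome measure section describes the battery as highly reliable with little practice effect, which suggests a higher r, although no figure is given. This also stands, and the loss should be quoted as a range.

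**The plan's own power is not threatened.** A reader might infer that real power is already below the stated figure. The documents do not establish that here: on f = .25 and r = .5, the G*Power default gives .968 before any change. The lower powers in the working come from substituting the cited d of about 0.5. Whether f = .25 is a realistic effect is a different question.

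**Multiple imputation.** A reader might also infer that the planned F-test combines badly with multiple imputation. It does not for the primary comparison: a 1-df interaction is a regression coefficient on change and pools by Rubin's rules as readily as an ANCOVA coefficient.

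**More than one sentence would change.** Group-by-time hypotheses recur across the outcome sections, and the power statement is built on the interaction. This stands, but the work is editorial.

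**Conclusion.** The planned primary analysis is valid, and it is unbiased over randomisations; nothing here supports a claim of bias. Its weakness is lost efficiency, together with greater sensitivity to a chance baseline difference in MCCB, which is plausible with about 30 per arm and no stratification described. The reason given for the choice does not exclude the better analysis.

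The size depends on a correlation the document only bounds: at most one third more patients at r = .5, falling to 5% at r = .9. In power terms the gain is .968 to .993 on the plan's own inputs. If the effect is nearer the cited 0.5 SD, it is .48 to .59 at r = .5 and .85 to .89 at r = .8. These figures rest on 1:1 allocation, equal SDs at both times and two-sided alpha .05. This is a free improvement and not a defect that invalidates the trial.

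**What to change.** - **Primary analysis:** fit a linear model for the 6-month MCCB composite with treatment, baseline MCCB composite, age and gender (or a baseline-adjusted mixed model on the follow-up visits). Report the adjusted CRT minus TAU difference with its 95% confidence interval.
- **Secondary outcomes:** use each outcome's own baseline in the same way. For the HCR-20 dynamic items and the DUNDRUM scales, measured only at baseline and 8 months, the response is the 8-month score.
- **Sensitivity analysis:** retain the repeated-measures interaction.
- **Text:** replace the rationale under Proposed analysis. Align the group-by-time wording in the sections on global cognition, cognitive domains, real world functioning, psychiatric symptoms, violence risk, and programme completion and recovery. Restate the power calculation for the adjusted comparison, naming the difference in SD units and the assumed r.

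The cost is rewording and one recalculation. No new data are needed, since baseline MCCB is already measured. The change should be made before outcome data are seen by arm.
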